#### The Control Arm

Participants in the control arm will also be recruited from those who are suspected of TB and screened using sputum examinations. The changes in the relevant registers will be made to record the status of nicotine use and health professionals will be given instructions on recording it on-site. The TB DOTS facilitators in control diagnostic centres will be provided with patient education leaflets to be given out to all patients recruited in the study. Apart from recording their status of nicotine use and arranging follow up at week 1 and 5, they will be provided usual care. No other components of the intervention will be delivered. We do not anticipate a significant risk of contamination, i.e. patients moving from one diagnostic centre to another, due to the geographical spread of facilities, and because no publicity will be produced regarding the availability of the treatment package in other facilities. In addition, we do not anticipate a significant benefit (other than what has been recorded previously in controls) in the control arm given that asking about nicotine use and providing information leaflets, are not, by themselves, sufficient to lead to stopping nicotine use.

#### Outcomes

These are as follows[30]:

1. Point abstinence at 4 weeks: The proportion of trial participants who have completely given up all forms of nicotine use at four weeks after the completion of bupropion and/or brief psychological intervention

2. Continuous abstinence up to 6 months: Proportion of trial participants who remained abstinent from 4 weeks onwards up to six months

3. We will also measure tobacco use e.g. number of cigarettes smoked per day to estimate any reduction in tobacco use secondary to the intervention

4. Secondary outcomes will include incidence of various adverse affects secondary to therapy

5. Economic outcomes will be assessed in terms of healthcare cost to get one person to stop smoking at four weeks. Healthcare cost will include the treatment cost, the average duration of health professionals' time spent with the patients during assessment, advice and counselling.

6. Process outcomes will include: the proportion of tobacco users who decide to quit and registered to receive 'five steps to quit' intervention; and the proportion of people registered who continue follow-up for the full period planned

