#### Delivery of the intervention

We propose to use a systematic, standardised approach to deliver 'five steps to quit' to make it effective and equitable[30]. It is envisaged that the intervention will be primary delivered by the TB DOTS facilitator based in the diagnostic centre with the help and under the supervision of the primary care doctor (Table 1). He will assess patients' eligibility for the study and send them to the TB DOTS facilitator for further assessment. All eligible patients will be provided with verbal and written information about the study and invited to participate. Patients who agree to take part will be taken through different components of the 'five steps to quit' programme in two appointments. Patients in intervention arm 1 will also be offered therapeutic option (Bupropion) and such patients will be referred to the primary care doctor for assessing suitability and prescribing Bupropion.

**Table 1 T1:** Follow up and contacts with health professionals

Trial arms	First contact	FU at week 1	FU at week 5	FU at week 8	FU at week 25
Intervention 1 (brief psychological intervention + therapeutics)	Assess eligibility at the laboratory	TB DOTS facilitator	TB DOTS facilitator	TB DOTS facilitator	TB DOTS facilitator
	TB DOTS facilitator	Doctor	Doctor (if necessary)		
	Doctor				
Intervention 2 (brief psychological intervention only)	Recruitment at the laboratory	TB DOTS facilitator	TB DOTS facilitator		TB DOTS facilitator
	TB DOTS facilitator				
Control (usual care + leaflet)	Recruitment at the laboratory	TB DOTS facilitator	TB DOTS facilitator		TB DOTS facilitator
	TB DOTS facilitator				

The TB DOTS facilitators and primary care doctors will be given a training course (using training manual) on the "five steps to quit" programme on the use of desk-guide and focusing on[30]:

• The scientific basis of the intervention

• Techniques to enquire about the status of tobacco use

• Providing brief advice on the benefits of stopping its use through visual images

• Approaches to assess nicotine dependence and motivation to quit

• Using this motivation to propose various treatment options explaining their pros and cons

• Training in the use of available pharmacotherapies and other cognitive-behavioural strategies

• The procedure for follow-up and other technical and organisational aspects.

• Familiarity with the recording and reporting system such as revised records and new tools

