#### Data collection

Our pilot study will determine the feasibility of our proposed tools to gather patient details and their status of nicotine use at various appointments. The modified tools will include:

1. 'Five steps to quit" intervention cards and register

2. A separate tobacco use questionnaire/register to record smoking status and motivation to quit

These approaches will allow us to record demographic details including gender, socio-economic status, presence of other smokers in the house and workplace, number of children at home, status of nicotine use, motivation level, type of therapy offered, extent to which therapy was used, adverse events and abstinence at different end points. We would adapt some of the tools already well described in the existing literature[30].

Patients who are subsequently diagnosed with TB will be followed up regularly for their TB treatment and the outcomes relevant to this study will be recorded during those visits. Trial participants who are diagnosed as not having TB and being given any of the three forms of therapy will be asked to follow up at the intervals specified. Controls not diagnosed with TB and received only usual care and a leaflet will be asked to return at 4 weeks to review their respiratory condition and to assess their status of nicotine use. Attrition is a potential problem. After piloting in phase 2, patients' mobile phone numbers will also be recorded and those who are lost to follow up will be contacted via their mobile phones to assess their status of nicotine use. A high proportion of Pakistanis possess mobile phones irrespective of socio-economic status.

Similarly, at six months in both intervention and control arms, all patients who stopped tobacco use will be contacted either via their mobile phones or landlines to assess their smoking status. According to our estimate this number will approximately be at least 264.

In order to estimate the average time spent by health professionals in delivering 'five steps to quit' intervention, our research officer will spent a day at each centre to measure and record this time.

We will also record the gender and status of nicotine use among all health professionals giving advice and include a column in the above patient record tools to record which health professional delivered which element of the package.

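### The only safety outcome is worded as effects of therapy, so as written it depends on attribution and does not use the two non-drug arms as a background rate

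*Protocol article*

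**What the plan says.** Under Objective 3, Outcomes, item 4 reads "Secondary outcomes will include incidence of various adverse affects secondary to therapy". It is the only safety item in that list. It names no events, assessor, time window or arms.

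The Data collection section names two tools. One is the "intervention cards and register" of the five-step programme. The other is "A separate tobacco use questionnaire/register to record smoking status and motivation to quit". The items these approaches will record include "extent to which therapy was used, adverse events and abstinence at different end points". Here the adverse events carry no causal qualifier and no arm restriction.

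Bupropion belongs to one arm: "Patients in intervention arm 1 will also be offered therapeutic option (Bupropion"). Arm 2 receives the same programme without the drug. Control receives usual care and a leaflet. For control, the section on that arm says "The changes in the relevant registers will be made to record the status of nicotine use" and "Apart from recording their status of nicotine use and arranging follow up at week 1 and 5, they will be provided usual care". Data collection adds that controls without TB return at 4 weeks for a respiratory review and an assessment of nicotine use. Neither place mentions adverse events.

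The Data analysis section compares arms on abstinence and on reduction in tobacco use. It names no comparison of adverse events.

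**The concern.** An outcome limited to effects of therapy puts a causal judgement before the count. Three features of this trial make that judgement unreliable.

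- **Symptoms are common for other reasons.** All participants have coughed for three weeks or more. By the article's own ratio of suspects to diagnosed cases, about one in ten has TB, and those diagnosed start anti-TB treatment.
- **The judgement is made with knowledge of the arm.** Centres are randomised and only arm 1 centres offer the drug.
- **Opportunities to record an event are unequal.** Patients on treatment in arm 1 have an extra visit at week 8, and doctor contacts appear in Table 1 for arm 1 only.

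What is at stake is whether the trial can say if offering bupropion in this population adds adverse events. An event wrongly put down to TB or its treatment would not be counted. One wrongly put down to the drug could not be set against a background rate. The randomised design supplies such a rate in two arms, but the stated outcome does not call on it.

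**Working it through.** The article gives no adverse-event rate, margin or safety sample size, so there is no figure of the plan's own to reproduce. The check is a reading of the sections side by side, followed by an illustration of what an all-events comparison could deliver.

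**Sections side by side**

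| Question | Where | What is stated |
|---|---|---|
| What counts? | Outcomes, item 4 | Effects resulting from therapy |
| What is recorded? | Data collection | Adverse events, unqualified, no arm named |
| What is done in control? | The Control Arm; Data collection | Nicotine status, follow-up at weeks 1 and 5, usual care; respiratory review at 4 weeks if no TB |
| Who attributes? | Delivery of the intervention | No one is named. Follow-up is mainly with the TB DOTS facilitator; doctors see arm 1 patients at some contacts |
| What is compared? | Data analysis | Abstinence and tobacco use |

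Item 4 and the list of recorded items therefore differ in scope. If events were recorded in every arm, item 4 read literally would still leave out those not attributed. In control there is no therapy beyond usual care and a leaflet to attribute them to.

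**Shared visits.** Table 1 gives all three arms a facilitator contact at weeks 1, 5 and 25. However, Data collection describes the six-month contact as a call to patients who stopped tobacco use. Only weeks 1 and 5 can safely be treated as common to all participants.

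**Precision of an all-events comparison.** Inputs from the article: 11 centres per arm, 50 recruited per centre (550 per arm) or 40 completing (440 per arm), ICC 0.036. Assumptions: event rates of 20% in arm 1 and 15% in a non-drug arm, and an ICC for adverse events equal to the one the article uses for its quit-rate sample size.

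- Unclustered half-width: 1.96 × √[(0.20×0.80 + 0.15×0.85)/550] = 1.96 × √(0.2875/550) = 0.0448, or 4.48 points.
- Design effect at 50 per centre: 1 + 49×0.036 = 2.764, square root 1.663.
- Clustered half-width: 4.48 × 1.663 = 7.45 points.
- With 440 completers: design effect 1 + 39×0.036 = 2.404. Half-width 1.96 × √(0.2875×2.404/440) = 7.8 points.

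Range over the assumed ICC (550 per arm, 20% v 15%): ICC 0 gives 4.5 points. ICC 0.01 gives a design effect of 1.49 and 5.5 points. ICC 0.036 gives 7.45 points.

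Range over the assumed background rate (550 per arm, ICC 0.036, 5-point excess): 10% v 5% gives 5.2 points, 15% v 10% gives 6.5, and 25% v 20% gives 8.2.

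A 5-point excess is not resolved in any of the clustered cases shown. With 440 per arm and ICC 0.036, power over backgrounds of 5% to 20% is 44% down to 21% for a 5-point excess, and 89% down to 60% for a 10-point excess. Only patients who wish to quit and are referred are prescribed the drug, so an excess averaged over the whole of arm 1 would be smaller than the excess among those treated.

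**The case against.** The best counter-argument is that item 4 is being read too literally. The item above it in the same list speaks of a reduction in tobacco use secondary to the intervention, and Data analysis shows that this is assessed by estimating it in the arms and comparing them. The phrase in item 4 may likewise mean only resulting from therapy, to be judged by comparison. This stands in part: a case-by-case causal filter is a plausible reading, not the only one. But Data analysis extends the comparison to tobacco use and not to adverse events, so the text does not settle the matter.

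A reader might also infer stronger claims that the document does not support.

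- **That adverse events are not collected in control.** This would be an inference from silence. The sentence "No other components of the intervention will be delivered" concerns care, not data capture, and Data collection names no arm. Collection in control is not described, but neither is it excluded.
- **That there is no comparator.** Arm 2 has the same programme without the drug, and the intervention cards would plausibly cover it. The comparators exist; the stated outcome does not use them. Arm 2 is not identical in follow-up, since its contact schedule differs.
- **That the prescribing doctor decides attribution.** No section assigns that task to anyone.

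Finally, an article may leave checklists, assessors and tabulations to the full protocol or analysis plan. That is fair, and their absence is not the point here. The point is the wording of a stated outcome and its mismatch with another section.

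**Conclusion.** The point holds as a matter of definition. The only listed safety outcome is worded as effects of therapy, a different section records adverse events in general, and the described control contacts mention none. As written, the outcome rests on attribution by an unnamed, unblinded assessor in patients who all have respiratory symptoms. It makes no stated use of two concurrent non-drug arms, and ascertainment is richer in arm 1.

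It does not follow that the trial could not show harm at all, or that control data will not exist. The effect on the results cannot be sized from the document, because no event rate is given. Rewording would remove the dependence on attribution, but it would not make the trial sensitive to small excesses. The half-width of about 7.45 points rests on the assumed 20% v 15% and on borrowing the quit-rate ICC. This is a secondary outcome, so the primary abstinence comparison is untouched, but the change is worth making.

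**What to change.** Reword item 4 as the proportion of participants with each adverse event irrespective of attribution, and bring Data collection and The Control Arm into line with it.

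- Ask the same short questions in all three arms at the shared week 1 and week 5 visits. Add week 25 only if all participants are contacted then, not just those who stopped.
- Compare by arm, with allowance for clustering by centre.
- Report attribution to therapy, and events found only at the extra arm 1 contacts, as separate descriptive items.

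The cost is an amended outcome line, a short checklist added to the register, and a few minutes per visit in arm 2 and control. No change to treatment or its management is involved.

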#### Data collection

Our pilot study will determine the feasibility of our proposed tools to gather patient details and their status of nicotine use at various appointments. The modified tools will include:

1. 'Five steps to quit" intervention cards and register

2. A separate tobacco use questionnaire/register to record smoking status and motivation to quit

These approaches will allow us to record demographic details including gender, socio-economic status, presence of other smokers in the house and workplace, number of children at home, status of nicotine use, motivation level, type of therapy offered, extent to which therapy was used, adverse events and abstinence at different end points. We would adapt some of the tools already well described in the existing literature[30].

Patients who are subsequently diagnosed with TB will be followed up regularly for their TB treatment and the outcomes relevant to this study will be recorded during those visits. Trial participants who are diagnosed as not having TB and being given any of the three forms of therapy will be asked to follow up at the intervals specified. Controls not diagnosed with TB and received only usual care and a leaflet will be asked to return at 4 weeks to review their respiratory condition and to assess their status of nicotine use. Attrition is a potential problem. After piloting in phase 2, patients' mobile phone numbers will also be recorded and those who are lost to follow up will be contacted via their mobile phones to assess their status of nicotine use. A high proportion of Pakistanis possess mobile phones irrespective of socio-economic status.

Similarly, at six months in both intervention and control arms, all patients who stopped tobacco use will be contacted either via their mobile phones or landlines to assess their smoking status. According to our estimate this number will approximately be at least 264.

In order to estimate the average time spent by health professionals in delivering 'five steps to quit' intervention, our research officer will spent a day at each centre to measure and record this time.

We will also record the gender and status of nicotine use among all health professionals giving advice and include a column in the above patient record tools to record which health professional delivered which element of the package.

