Training of TB DOTS facilitators will also focus on the brief counselling techniques based on cognitive-behavioural model[32]. A simple desk-guide will be provided with simple algorithms and instructions for health professionals to follow "five steps to quit" programme. This will also include glossy images to support patients in understanding the benefits of stopping smoking. The TB DOTS facilitator, for all eligible patients, will be responsible for:

• Assessment of the status of their tobacco use through a checklist of questions

• Advising on benefits of quitting using visual and written educational material

• Assessment of willingness for inclusion in the study and motivation to quit using a simple scoring card

• Registration and recording of demographics and contact details

• Structured counselling using a desk guide and patient planner

• Giving a quit date after a week

On the subsequent visit in a week's time, TB DOTS facilitator will be responsible for

• assessing the status of their tobacco use

• Sharing their experience of attempting to quit, listen to the difficulties they had and providing supportive counselling to help cope with the difficulties

• Referring them to doctor if the intervention arm includes therapeutic option

• Arranging follow up in a month's time.

At follow ups at week 5 and 25, TB DOTS facilitators will be responsible for

• Reassessing status of nicotine use and recording it in the tobacco use questionnaire/register

• Reviewing treatment and other options

• Rearranging follow up as per desktop guide.

In the intervention arm 1, the primary care doctors, in addition to supervising TB DOTS facilitators, will be responsible for assessing and prescribing therapeutics (Bupropion) to patients who wish to quit and are being referred by the TB DOTS facilitators. All patients on treatment will have an additional follow up visit at week 8. In intervention arm 2, doctors will be only responsible for supervising TB DOTS facilitators. They will be provided with the appropriate training and relevant materials.

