#### Data analysis

Our research officer will collate data from all health centres on a monthly basis and feed them into a database created via SPSS kept on a mobile computer. There will be an assessment of smoking status by intervention category, analysed on an intention to treat basis. The point abstinence will be compared between the intervention and control arms at 4 weeks after the completion of the treatment and in controls 4 weeks after they were given the leaflets. Further analyses will include the comparison of continuous abstinence at six months between the two arms. We will also estimate reduction in tobacco use in both trial arms and compare to detect any difference. Missing data on the outcomes will not be inputted. Secondary analyses will investigate the use of, and adherence with, the various forms of therapy. Further sub-analyses will be carried out to detect differences in outcomes according to a number of variables such as gender of the participants and providers, smoking status of the provider, socio-economic status, existence of other smokers in the house or workplace and presence of children at home. We are mindful that sample size estimation was not based on these sub-analyses and therefore we may not be able to detect small differences in the outcomes according to these variables.

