##### Attrition Rates

The sample size calculation incorporates an attrition rate of 20%. This is based on the observations made in the trial of tobacco control in TB patients in Sudan where less than 20% patients defaulted over a period of six months. An intention to treat analysis will account for any non-differential loss to follow up. As part of DOTS, patients with diagnosed TB are generally followed up for a period of six months. However, follow up of non-TB patients will be arranged as part of the trial.

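### The planned telephone calls are described as covering tobacco status but not adverse effects, so adverse-effect incidence may be underestimated if patients are lost because of them

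*Protocol article*

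**What the plan says.** All of this is in the protocol article, under Objective 3.

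- **Outcomes:** "Secondary outcomes will include incidence of various adverse affects secondary to therapy".
- **Data collection, tools:** the intervention cards, register and tobacco use questionnaire are to capture, among other items, "type of therapy offered, extent to which therapy was used, adverse events and abstinence at different end points".
- **Data collection, patients found to have TB:** they are seen regularly for TB treatment, and "the outcomes relevant to this study will be recorded during those visits".
- **Data collection, patients who stop attending:** "those who are lost to follow up will be contacted via their mobile phones to assess their status of nicotine use".
- **Data collection, six months:** "all patients who stopped tobacco use will be contacted either via their mobile phones or landlines to assess their smoking status".
- **Delivery of the intervention:** contacts after the first are at weeks 1, 5 and 25. In addition, "All patients on treatment will have an additional follow up visit at week 8".
- **Attrition Rates:** "The sample size calculation incorporates an attrition rate of 20" per cent.
- **Data analysis:** "Missing data on the outcomes will not be inputted".

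**The concern.** Attrition is recognised as a problem and a remedy is provided, but the stated purpose of that remedy serves one outcome and not another. A centre working from this text would telephone a patient on bupropion who had stopped coming, record whether he uses tobacco, and have no instruction to ask about adverse effects. The six-month call has the same stated purpose and goes only to patients who have stopped using tobacco.

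This matters because loss may be informative for safety: an adverse effect is a plausible reason not to return. If so, the missing safety data are concentrated in the patients most likely to have had an event, and the analysis does not repair this, since missing outcomes are not imputed. The article also states no denominator for the incidence. Its Discussion says the results are meant to support adoption by the national TB and tobacco programmes, so a safety figure drawn mainly from patients who kept attending could mislead.

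**Working it through.** **1. Which contacts have a stated provision for each outcome**

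| Contact | Tobacco status | Adverse effects |
|---|---|---|
| Trial visits (cards, register, questionnaire) | yes | yes, listed among the recorded items |
| TB treatment visits (patients with TB) | yes | yes, as a study outcome |
| Call to patients lost to follow-up | yes | not mentioned |
| Six-month call (patients who stopped) | yes | not mentioned |

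The TB visits probably cover few recruits. Under Number of individuals per facility, suspects are about ten times the patients diagnosed. If recruits follow that ratio, about one in ten has this route and the rest depend on trial visits or the call.

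**2. The plan's own attrition figure**

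Cluster size 40 and 80% completing (Sample size): 40 / 0.80 = 50 recruited per centre, which reproduces the plan. Expected non-completers are 50 × 0.20 = 10 per centre. In one arm of 11 × 50 = 550 patients that is 550 × 0.20 = 110.

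**3. Possible understatement**

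The article gives no adverse-effect rate, so the rates here are assumptions. Let d be the proportion lost, p the incidence in attenders and k·p the incidence in lost patients. Suppose nothing is known about adverse effects in lost patients.

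- True incidence = (1 − d)·p + d·k·p = p·[1 + d(k − 1)]
- Reported, patients seen as denominator = p, so reported/true = 1 / [1 + d(k − 1)]
- Reported, all recruited as denominator (lost counted as event-free) = (1 − d)·p, so reported/true = (1 − d) / [1 + d(k − 1)]

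The rate p cancels, so only d and k matter. At d = 0.20:

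| k | 1 + d(k − 1) | Patients seen | All recruited |
|---|---|---|---|
| 1 | 1.0 | 1.00 | 0.80 |
| 1.5 | 1.1 | 0.91 | 0.73 |
| 2 | 1.2 | 0.83 | 0.67 |
| 3 | 1.4 | 0.71 | 0.57 |

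Example with p = 20% and k = 2: true 0.8 × 20% + 0.2 × 40% = 24%; reported 20% (patients seen) or 0.8 × 20% = 16% (all recruited).

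**4. Sensitivity to the loss rate**

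Over k = 1 to 3, a loss of 10% gives 1.00 to 0.83 (patients seen) and 0.90 to 0.75 (all recruited). A loss of 30% gives 1.00 to 0.63 and 0.70 to 0.44.

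**5. Why step 3 is a ceiling for a given d and k**

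It assumes that a lost patient contributes no safety data. In fact, events before the last attended visit are recorded. The 20% is non-completion by six months, so a patient who misses only week 25 counts as lost but has attended weeks 1, 5 and, if on treatment, 8. Also, bupropion is offered only in arm 1, to patients who wish to quit, are referred and are judged suitable. Lost patients who never took it are correctly free of effects of that drug.

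**The case against.** The strongest reply is that this reads too much into one phrase. The article says why lost patients are telephoned; it neither lists the questions nor restricts them. It condenses a fuller protocol, and a call form is the kind of detail left there. It also seems to use nicotine status as shorthand for follow-up generally: the facilitator's listed duties at weeks 5 and 25 do not mention adverse events either, yet the tools do record them, and nothing confines those tools to face-to-face use.

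Much of this stands. A reader might infer that adverse effects are never asked about after loss, or that calls are limited to nicotine use; the text says neither. A reader might also infer that the reported incidence is bound to be too low. That does not follow: with equal rates in lost and attending patients and patients seen as the denominator, there is no understatement at all. Nor can the 110 expected non-completers in arm 1 be read as treated patients without safety data, for the reasons in step 5 of the working.

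The reply does not remove the gap. The article does more than leave the calls unspecified: it gives each a purpose, and in both it is tobacco use. Visits have an explicit provision for adverse events through the listed items, and the calls have none.

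**Conclusion.** The point holds in a limited, conditional form. As described, follow-up by telephone recovers abstinence but makes no provision for adverse effects arising after the last attended visit, although their incidence is a stated outcome. Ascertainment is incomplete rather than absent.

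The incidence may be underestimated under either of two conditions: loss is related to adverse effects, or lost patients are counted as event-free. At 20% loss and an assumed rate ratio of 1 to 3, the understatement is at most 0% to 29% with patients seen as the denominator and 20% to 43% with all recruited. The actual size cannot be computed, because the article gives neither an adverse-effect rate nor a link between adverse effects and loss. The loss rate is itself uncertain: it comes from TB patients in Sudan, whereas follow-up of patients without TB has to be arranged by the trial.

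The change is worth making because the call is already planned and the correction is cheap.

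**What to change.** Amend Data collection so that the call to patients lost to follow-up also asks, in every arm and with the same questions as at visits, about adverse events since the last contact and whether they led to stopping therapy or attendance. Using the same questions in all arms keeps ascertainment comparable. Report adverse-effect incidence with the number of patients actually asked as the denominator.

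The cost is a few more questions in an existing call and extra fields on the form. Calls will be slightly longer and recall by telephone is less exact than at a visit. Patients who cannot be reached remain unknown, and the stated denominator makes that visible.
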